### Recruitment

The recruitment is carried out by a designated study team of the Department of Neurology, University Hospital Ulm, Germany, during the in-patient stay of patients eligible for participation in Groups 2 and 3. Patients with CSVD without a current stroke are recruited at our specialized outpatient clinic for CSVD and cerebrovascular diseases. As of June 11th, 2026 6 male patients and 3 female patient were enrolled. Of those, 5 (56%) presented with acute territorial stroke and were recruited in Group 3, 3 had a lacunar stroke and were assigned to group 2 (33%) and one further participant without acute stroke was recruited into group 1 (11%). The median age was 68 years with a minimum of 52 and a maximum of 85 years.

### Demographics

For study participants, the following demographics and patient characteristics is collected: year of birth, sex (male/female/non-binary), ethnicity, International Standard Classification of Education (ISCED [22]), level, earliest/current profession/retirement according to International Standard Classification of Occupations (ISCO) classification [23], family history of stroke, myocardial infarction, peripheral artery disease, venous thromboembolism, CSVD, known or obtained genetic disorders or test results respectively in the study participant or first-degree relatives (coded as negative/positive/not informative).

Furthermore, we gather information about the current living situation (living independently in a single/couple/family household/in a nursing home), and the marital and parental status. We ask for concurrent malignancy (present/absent) and, if present, specify the type and staging results. In addition, the history and current presence of cardiovascular risk factors is taken (arterial hypertension, diabetes, current/past smoker/hypercholesterolemia/family history as stated above).

### Parameters

In participants with known CSVD, age at disease onset and past brain MRI results will be collected. For each patient, at each visit, the following clinical parameters will be recorded: (1) current global or focal neurological symptoms (e.g. subjectively evident memory disorders, gait disorders, dysarthria, focal motor or sensory symptoms, bladder dysfunction, dizziness/vertigo), those symptoms are summed up using the National Institutes of Health Stroke Scale (NIHSS) is a standardized 15-item neurological examination tool used by healthcare professionals to quantify acute stroke severity and monitor neurological changes and the modified Rankin Scale (mRS), a 6-point scale for measuring the degree of disability or dependence in the daily activities (2) current blood pressure, heart rate, peripheral Sp02 saturation, (3) height and body weight to calculate the body mass index.

### Magnetic resonance imaging

Brain imaging is conducted at the University Hospital, Ulm, Department for Radiology, Section of Neuroradiology at a 1.5-T or 3-T MRI system (MAGNETOM Vida, Siemens Healthineers, Erlangen, Germany). Imaging includes the following sequences: DWI, 3D fluid attenuated inversion recovery (3D-FLAIR), susceptibility-weighted imaging (SWI) and/or T2* imaging, 3D-T2-weighted imaging, T1-weighted Magnetization-Prepared Rapid Gradient Echo (MPRAGE), and time-of-flight MR angiography (TOF-MRA).

On the 1.5-T system (MAGNETOM Altea, Siemens Healthineers, Erlangen, Germany) the 3D-FLAIR is acquired sagittally with a voxel size of ~ 1.0 × 1.0 × 1.4 mm^3^ (reconstruction voxel: ~0.5 × 0.5 × 1.0 mm^3^, 160 slices; TR = 7000 ms, TE = 433 ms; flip angle = 120°).

If possible (e.g., compliant patient, no emergency setting), advanced sequences will be added to the protocol, such as arterial spin labeling (ASL), resting-state functional MRI (rs-fMRI), or mapping sequences. On the 1.5-T system (MAGNETOM Altea, Siemens Healthineers, Erlangen, Germany) the 3D-FLAIR is acquired sagittally at 0.49 × 0.49 × 1.0 mm (acquired matrix 512 × 512, 160 slices; TR/TE 7000/433 ms; flip angle 120°). The 1.0 mm slice thickness meets, and the acquired 0.49 mm in-plane resolution exceeds the ~ 1 mm isotropic resolution referenced by STRIVE-2 for structural imaging.

For visual detection of ischemic lesions, a standard diffusion-weighted sequence will be used with whole-brain coverage. In addition, on the 3-T system (MAGNETOM Vida, Siemens Healthineers, Erlangen, Germany), a dedicated additional DWI sequence for advanced diffusion analyses (e.g., fractional anisotrophy (FA), the peak width of skeletonized mean diffusivity (PSMD)) will be added according to the following parameters: echo-planar imaging (EPI) with simultaneous multi-slice (SMS) acceleration using a factor = 2, no phase Partial Fourier, acquisition in transversal orientation, slice thickness = 3 mm, acquisition / reconstruction voxel size = ~ 2 × 2 × 3 mm^3^, repetition time (TR) = 3100 ms, echo time (TE) = 104 ms, fat saturation (strong), 65 diffusion directions, three diffusion weightings (b = 0 s/mm², b = 1000 s/mm², and b = 2000 s/mm²), and phase encoding direction = A > P, with an acquisition duration < 10 min. In addition, a short analogous DWI sequence with phase encoding direction = P > A will be added (to be able to correct for geometric distortions), with an acquisition duration < 1 min.

Features of CSVD are determined according to STandards for ReportIng Vascular changes on nEuroimaging (STRIVE) criteria [2]. This will be conducted by trained (neuro-)radiologists and vascular neurologists considering the above-mentioned sequences (especially FLAIR, T1-weighted MPRAGE, DWI, and SWI or T2*). Interrater reliability will be calculated for the determined volume of CSVD, the presence or absence of cerebral microbleeds, lacunes, and perivascular spaces using a set of randomly selected patients.

To account for scanner differences between acquisitions, WMH segmentation will be performed using a FLAIR-only automated in-house pipeline based on the half-Gaussian mixture model described by Igwe et al. [25], which models log-transformed above-mode FLAIR intensities as a two-component mixture: a half-Gaussian for normal-appearing white matter and a full Gaussian for WMH, with all five parameters estimated via expectation-maximization. The original method was validated on a single scanner and timepoint; we extend it to longitudinal cross-scanner comparison by fitting the HGMM independently per timepoint on a shared white matter territory (intersection of both timepoints’ white matter labels), with a two-pass refinement that excludes candidate WMH from the fit pool to tighten the normal-appearing white matter model. Longitudinal change is estimated through paired voxel-wise contrast at the TP1 lesion boundary, corrected for scanner offset (estimated from stable white matter) and blur mismatch, rather than by subtracting two independent segmentations. Anatomical false positives are removed through automated exclusion. Acute DWI lesions identified on the baseline MRI were registered to FLAIR space andexcluded from the WMH volume calculations at baseline, 6-month, and 12-month follow-up. This procedure ensured that longitudinal WMH measurements represented chronic white matter disease burden, independent of the baseline acute infarct.

In the pilot cohort, baseline and follow-up FLAIR were acquired on different scanners and protocols, so standard endpoint WMH segmentation could not reliably separate true lesion change from scanner-induced contrast shifts. We therefore used a scanner-aware longitudinal pipeline designed to identify the FLAIR change as biological progression rather than scanner change artifacts. Since the prospective cohort is acquired on a stable, harmonized protocol, Deep WMH and Multi-site Auto-segmentation and Registration of Subcortical White Matter Hyperintensities (MARS)-WMH-derived segmentation will additionally be evaluated, with agreement to the manual reference quantified by Dice similarity coefficient and ICC.

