### Primary outcome

The primary outcome is the change in WMH volume based on brain MRI measurements.

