### Eligibility criteria

Patients are eligible as participants if (a) their age is ≥ 18 years and if (b) brain MRI provides evidence of CSVD, defined as WMH (Fazekas grade 1–3). Patients with Fazekas grade 1 will be included as well to cover all different stages of CSVD and because even a mild lesion load has been linked to neurocognitive impairment [21]. In case of uncertainty about the aetiology of WMH, diagnostics to rule out inflammatory diseases or genetic small vessel diseases are planned. Furthermore, (c) patients must be assigned to one of the following groups based on MRI findings: Group 1: CSVD without evidence of an acute ischemic stroke, Group 2: CSVD with acute lacunar ischemic stroke, defined as singular diffusion-weighted imaging (DWI)-hyperintense, apparent diffusion coefficient (ADC)-hypointense lesion on brain MRI with a diameter of maximum of 2.5 cm, or group 3: CSVD with acute territorial ischemic stroke pattern on MRI. All patients must be (d) able to provide written informed consent and (e) have sufficient German language skills to understand study procedures and assessments. The requirement for sufficient German language skills is necessary to ensure valid neuropsychological assessments. However, this criterion may introduce selection bias and may limit the generalizability of the study findings.

Inclusion criteria are as follows:

Age ≥ 18 years.Evidence of CSVD on brain MRI, defined as the presence of WMH (Fazekas grade 1–3).Assignment to one of the defined study groups based on MRI findings.Ability to provide written informed consent.Sufficient German language skills.

Exclusion criteria are as follows:

Alternative plausible causes of WMH other than CSVD.Known neurodegenerative diseases.Acute or recent traumatic brain injury.Contraindications to MRI.Pregnancy or breastfeeding.Expected life expectancy of less than one year.Inability to comply with study procedures or follow-up visits.Severe renal insufficiency with an estimated glomerular filtration rate <15 ml/min

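### As described, new WMH separate from any baseline lesion have no stated route into the primary WMH volume change

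*Protocol article*

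**What the plan says.** Protocol article, Primary outcome: "The primary outcome is the change in WMH volume based on brain MRI measurements". The abstract agrees. Neither limits the outcome to growth of lesions already present.

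Protocol article, Postprocessing, on how change is measured:
- The method is planned for this cohort, not only reported from the pilot: "WMH segmentation will be performed using a FLAIR-only automated in-house pipeline".
- Change is obtained as follows: "Longitudinal change is estimated through paired voxel-wise contrast at the TP1 lesion boundary", corrected for scanner offset and blur mismatch, and "rather than by subtracting two independent segmentations".
- The mixture model is fitted at each timepoint on a shared territory, the "intersection of both timepoints’ white matter labels".
- Acute infarcts seen at baseline are removed "from the WMH volume calculations at baseline, 6-month, and 12-month follow-up".
- Two other segmentation tools are to be evaluated in addition, for agreement with a manual reference. Neither is named as the source of the primary change.

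Fig. 1, which shows pilot participants, labels TP1 as baseline and TP2 as 12 months. Table 2 schedules MRI at 0, 6 and 12 months. Methods of analyses plans individual slopes from linear mixed-effects models. Sample size bases its sensitivity figures on paired manual volumetry in 17 pilot patients.

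**The concern.** WMH volume can rise in two ways: existing lesions expand, or new foci appear elsewhere. An estimator that reads contrast at the edge of baseline lesions sees the first. It has no place to see the second, and the alternative that would count it, the difference between two segmentations, is expressly set aside. The stated estimator is therefore narrower than the stated outcome.

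This bears on the study's own questions. The reach of a boundary measure depends on how much lesion edge a patient has at baseline. Patients with little WMH are enrolled on purpose: "Patients with Fazekas grade 1 will be included as well to cover all different stages of CSVD". The Introduction cites faster progression where baseline burden is higher, and a measure tied to baseline edges could contribute to such a pattern by construction. A biomarker that tracks burden could then look as if it tracks progression.

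There is also a question of which variable is analysed. A two-scan change score and a series of three per-visit volumes are different data, and the slopes need the second.

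**Working it through.** **1. Outcome against estimator.** Follow each kind of change through the method as written:

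| Change between scans | In WMH volume change? | Stated route into the pipeline's change? |
|---|---|---|
| Baseline lesion expands at its edge | yes | yes, boundary contrast |
| Baseline lesion shrinks at its edge | yes | yes, boundary contrast |
| New focus touching no baseline lesion | yes | none stated |

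The article also does not say how boundary contrast is converted to mL.

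**2. Change score against per-visit volumes.** The change method names two timepoints. The infarct exclusion refers to WMH volumes at three visits, Table 2 has three MRI visits, and the slopes need a value at each. Per-visit volumes could include new foci, but a slope through them is in effect a comparison of separate segmentations, which the change method rejects. The section therefore supports two different primary variables and does not choose between them.

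**3. What the sensitivity figures refer to.** Inputs from Sample size: mean change 5.30 mL, SD 6.03 mL, two-sided α = 0.05, power 80%, 60 enrolled and 60 × 0.75 = 45 completing per group. With z₀.₉₇₅ + z₀.₈₀ = 1.960 + 0.842 = 2.802:
- d_z = 5.30 / 6.03 = 0.88.
- Within-subject, d_z = 2.802 / √n: 0.362 at 60 and 0.418 at 45. Times 6.03 this is 2.18 and 2.52 mL.
- Between groups, d = 2.802 × √(2/n): 0.511 at 60 and 0.591 at 45. Times 6.03 this is 3.08 and 3.56 mL.

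These reproduce the stated 2.2–2.5 mL and 3.1–3.6 mL. The arithmetic is sound, but mean and SD both belong to manual volumetry. No mean or SD for the boundary measure is given.

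**4. Can the loss be sized?** Not from the documents. If a share f of true change lies in separate new foci, the measured change is (1 − f) × 5.30. For assumed f of 10%, 20%, 30% and 50% this is 4.77, 4.24, 3.71 and 2.65 mL. The effect on power depends on a second unknown, the SD of the boundary measure:
- SD held at 6.03: power for a true 3.6 mL between-group difference at 45 per group (noncentral t) falls from 80% to 71%, 61%, 50% and 29% for the same values of f.
- SD shrinking in the same proportion: (1 − f) × 5.30 / [(1 − f) × 6.03] = 0.88, so the standardised effect does not change.

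Both f and the SD behaviour are assumptions. The range shows only that the answer is open.

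**The case against.** The strongest reply is that the article does produce complete WMH volumes. The model is fitted separately at each timepoint, Fig. 1 shows full manual and automated segmentations at both scans, Postprocessing has trained raters measuring WMH volume, and volumes at three visits are mentioned. New foci could appear in any of these. This stands as far as it goes: a reader might infer that new lesions go unseen altogether, and the text does not support that. But none of these volumes is named as the source of the primary change, whereas the boundary contrast is described as the way longitudinal change is estimated.

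A reader might also infer that the 0–6 and 0–12 month comparisons use different territories, so that their changes do not add up. The documents do not say so. The intersection of labels is described only as where the mixture model is fitted, and no three-scan rule is given in either direction. On its own that would be detail an article may leave to the full protocol.

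A reader might further infer a large loss, nearly total in patients with few lesions. No figure supports this. WMH is an entry criterion, so every patient has some baseline lesion. Baseline burden by group is not reported, so a difference in bias between groups is possible but not shown.

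Finally, the study is exploratory and its tests are hypothesis-generating. That limits the consequence to the meaning of the endpoint. It does not remove the mismatch.

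**Conclusion.** The point holds in a limited form. As written, the change estimator leaves new WMH not contiguous with a baseline lesion without a route into a primary outcome defined as change in WMH volume. It also conflicts with the per-visit volumes in the same section and with the planned slopes, and it is written for two scans where three are scheduled. The quoted sensitivities of 2.2–2.5 mL and 3.1–3.6 mL describe manual volumetry and do not transfer directly to this estimator.

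The size of any loss cannot be derived from the documents, and whether territories differ between comparisons is not stated. The conclusion assumes that the pipeline is applied as Postprocessing describes it, which the future tense there supports. It should be corrected because it affects the validity and interpretation of the primary endpoint; no confirmatory sample size is at stake.

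**What to change.** Define one primary variable in mL that counts both boundary change and new separate WMH:
- Extend the offset- and blur-corrected paired contrast from the baseline lesion edge to the whole shared white matter, and count new clusters above a prespecified minimum size.
- Report boundary change and new-lesion volume as separate components as well as their sum.
- Use one territory per patient, formed from the scans that patient has, so that a missed 6-month scan does not exclude anyone. This matters with 25% drop-out expected.
- State that the slopes use this variable at each visit.
- Say that the sensitivity figures refer to manual volumetry.

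The cost is some extra processing within a pipeline already in hand and slightly more noise away from lesion edges, which the minimum cluster size limits. No further scans or visits are needed. Recruitment began in March 2026 and nine patients had been enrolled by 11 June 2026, so the definition can be settled before any 12-month scan of this cohort falls due.

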**Fig. 1 Fig1:**
[figure not shown]
Examples of longitudinal white matter hyperintensity (WMH) segmentation across scanner sessions, as performed in participants of the pilot trial. (**a**, **d**) Timepoint 1 (TP1, baseline brain MRI) and timepoint 2 (TP2, 12 months follow-up brain MRI) fluid-attenuated inversion recovery (FLAIR) images. (**b**, **e**) Manual WMH segmentation (green overlay) for TP1 and TP2, respectively. (**c**, **f**) Automated segmentation using a hyperintense Gaussian mixture model (HGMM) pipeline (red overlay) for TP1 and TP2, respectively. (g) TP1 white-matter intensity distribution (mode = 383). (**h**) TP2 white-matter intensity distribution (mode = 178). (**i**) Log-normalized intensity distributions of both timepoints, confirming alignment of the mode-matched peaks across scanner sessions

### Neurovascular diagnostics

Furthermore, neurovascular duplex sonography of the extracranial and intracranial cerebral arteries is conducted at study visits, including assessment of intima–media thickness and arterial impedance. For interpretation of atherosclerotic plaques in the carotid arteries, the Mannheim Carotid Intima-Media Thickness and Plaque Consensus will be applied [26].

### Biosamples

At all scheduled study visits, venous blood samples will be collected, processed, aliquoted, and stored in the biobank of the Department of Neurology according to established standard operating procedures. Laboratory analyses include a comprehensive panel of vascular, metabolic, inflammatory, and neurodegeneration-related parameters. Vascular and metabolic markers comprise lipid parameters (Low- and high-Density Lipoprotein (LDL, HDL), cholesterol, triglycerides, and lipoprotein(a)) as well as markers of glucose metabolism, including insulin and glycated hemoglobin (HbA1c). Cardiac biomarkers (troponin I or T) at baseline in groups 2 and 3 and inflammatory markers, including high-sensitivity C-reactive protein, interleukin-6, and interleukin-1 alpha, are assessed to characterize systemic vascular and inflammatory status [27].In addition, blood-based biomarkers reflecting central nervous system injury are analyzed, e.g. GFAP as a marker of glial activation, neurofilament light chain (NfL) as a marker of axonal damage, phosphorylated tau 217 (pTau217) as an exploratory neurodegeneration-related biomarker, and beta-synuclein as an exploratory synaptic marker.

CSF samples obtained as part of routine clinical care and based on clinical indication (e.g. to exclude inflammation or vasculitis) will be used for biomarker analyses, including total tau protein, phosphorylated tau, and amyloid-β1–42. In addition, endothelial cell–related biomarkers, including endothelin-1 and vascular cell adhesion molecule-1 (VCAM-1), are analyzed to capture endothelial dysfunction associated with cerebral small vessel disease [28, 29].

### Cognitive and functional diagnostics and outcomes

Neuropsychological examinations are included to assess cognitive function longitudinally. We perform a neuropsychological assessment at the baseline visit and at the 12 months follow-up, which is adapted to the current capacity of the study participant with a focus on attention, executive function, visual and verbal primary and working memory, as well as visuospatial function. Furthermore, MoCA will be performed at each study visit. We elaborated two different scenarios of neuropsychological assessments according to the capacity of the respective participants as the acute stroke pattern, clinical impairment (e.g. fatigue, resilience, dysarthria, blood-pressure variations, impairment due to acute stroke treatment) and pre-stroke morbidity can differ substantially. In patients with expected ability to undergo extended neuropsychology, the following tests are performed: TAP to assess alertness; the executive basic function/visual fluency using the 5-Point Test according to Regard and verbal fluency. We use the Rey Complex Figure to assess for visuospatial function and visual memory; for verbal memory, RBANS is applied and for verbal intelligence we perform a vocabulary test.In patients with low expected capacity for neuropsychological assessment, only the MoCA is carried out. Furthermore, MoCA is applied at each visit in its versions A-C.

The cognitive and functional outcome assessment is summarized in Table 1.

**Table 1 Tab1:** Cognitive assessment as per study protocol

Neuropsychological assessment				
Visits	1	2	3	4
	Screening and Baseline	Follow-up	Follow-up	End-of-Study
Months after enrollment	0	3	6	12
Assessment				
Basic NPA	x			X
MoCA	x	x	x	X
Extended NPA	x			X
TAP Alertness	(x)			(x)
5-Point Test according to Regard	(x)			(x)
Rey Complex Figure	(x)			(x)
RBANS	(x)			(x)
Verbal fluency Test	(x)			(x)

MoCA, Montreal Cognitive Assessment; NPA, Neuropsychological Assessment; RBANS, Repeatable Battery for the Assessment of Neuropsychological Status; TAP, Test of Attentional Performance; Assessments in parenthesis display optional study elements

### Functional neurological assessment

Participants undergo clinical assessment using the NIHSS and mRS. Furthermore, we will gather information about their quality of life (QoL), using the structured EuroQol 5 Dimension (EQ-5D) [29]. The functional abilities of daily life are further specified using the activities of daily living (ADL) and the instrumental activities of daily living (IADL). In addition, and to capture influences of CSVD and stroke on the preservation of abilities to work, data will be collected using the Work Ability Index (WAI).

